### Data analysis and power calculations

The Shapiro–Wilk and Levene’s tests will be used to determine normality and variance equality, respectively. Non-normal data will be log transformed. If the transformation does not produce a normal distribution, the effect of influential points in data analyses will be tested. If influential points change the interpretation of the results, they will be manually removed. Linear mixed models having group and time as fixed factors and patients as a random factor will be performed for each outcome (MADRS, clinical outcomes, hippocampal volume, brain-derived neurotrophic factor, cardiopulmonary parameters, lipid profile, and treatment costs) and domain (especially in clinical outcomes) [85]. In case an outcome presents pre-experimental period differences between groups, determined by a regular one-way ANOVA, an ANCOVA will be implemented having pre-experimental period values as covariates, group as a fixed factor, and patients as a random factor. An intention-to-treat analysis will also be performed in case of a high incidence of missing values, using linear mixed models; the first analysis will be performed removing the missing values, while the second analysis will be performed incorporating the missing data points to determine the impact of missing values in the overall results. Whenever a significant F-value is obtained, a post hoc test with a Tukey’s adjustment will be performed. In addition, within-group (pre- to post-changes) and between-group effect sizes will be calculated using Cohen’s d [86] for each outcome. Effect sizes will be classified as small (≤ 0.49), medium (0.50–0.79), and large (≥ 0.80). Finally, the level of significance adopted in the present study for all analyses will be *P* ≤ 0.05. Data will be presented as mean ± SD. SAS 9.2^®^ software (Institute Inc., Cary, NC, USA) will be used for the statistical analyses described. Considering the importance of the control of the error rates, typical error and coefficient of variation of the assessments will be performed under test and retest conditions in a sub-sample (10 subjects).

For the primary outcome (MADRS) the verification of status of depression (depressed, partial remission, full remission) and the number of patients in remission (< 10 points MADRS) will be verified [14, 87].

Power calculations were performed using data published by Kerling et al. [88] (effect size 0.25), who showed that an aerobic exercise program can positively change depression scores as assessed by the MADRS scale. The obtained sample size was 21 patients per group (power 0.85, alfa error 0.05, correlation between repeated measures of 0.8). Assuming a drop-out ratio of approximately 30%, we will determine 25 patients per group as appropriate.

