**Methods/design:**

Seventy-five medicated patients with depression will be recruited from a Basic Healthcare Unit to participate in this prospective, parallel group, single blinded, superiority, randomized controlled trial. Patients with depression according to DSM-V criteria will be balanced and randomly assigned (based on depression scores and number of depressive episodes) to a non-exercising control (C), CAE, and AEMC groups. The CAE and AEMC groups will exercise for 60 min, twice a week for 24 weeks (on non-consecutive days). Exercise intensity will be maintained between 12 and 14 points of the rating of perceived exertion scale (~ 70–80% of the maximum heart rate). The CAE group will perform a continuous aerobic exercise while the AEMC group will perform exercises with progressively increased motor complexity. Blinded raters will assess patients before and after the intervention period. The primary outcome measure will be the change in depression score measured by the Montgomery-Asberg Depression Rating Scale. Secondary outcomes will include measures of cognitive function, hippocampal volume, brain-derived neurotrophic factor expression, sleep parameters, cardiovascular risk parameters, suicidal behavior, functionality, and treatment costs.

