### Outcome measures – primary outcome

The MADRS scale [28] encompasses 10 items that assess apparent and reported sadness, inner tension, sleep and appetite changes, concentration difficulties, slowness, inability to feel, and pessimistic and suicidal thoughts. Nine items are based on the patient’s report and one on the psychiatrist’s observations. The higher the score, the greater the presence of depressive symptoms; scores range from 0 to 60 [62]. The MADRS scale will be applied in the pre- and post-intervention assessments.

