#### Cardiovascular risk

##### Overall cardiovascular score

The Brazilian Cardiovascular Prevention Directive recommends the use of the Global Cardiovascular Score [71] as an indicator of cardiovascular risk. For its calculation, age (ratings of − 9 to 8), total cholesterol (ratings of − 3 to 3), HDL-cholesterol (ratings of − 3 to 5), systolic blood pressure (ratings of − 3 to 3), a diagnosis of diabetes (ratings of 0 to 4), and whether the individual is a smoker (ratings of 0 to 2) are considered. After attributing the values of the respective outcomes, the sum of these results in a single value, which corresponds to cardiovascular risk. This ranges from less than 0 (no risk) to greater than 17 (cardiovascular event risk of 30%). Health professionals receive a booklet with details of such calculation from the Brazilian Ministry of Health [72].

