#### Clinical outcomes – scales of suicidal ideation, sleep, and BRIAN

The Columbia Suicide Severity rating scale distinguishes suicidal ideation from suicidal behavior. There are four subscales, namely severity of ideation (score of 0–5), intensity of suicidal ideation (score of 0–5), behavior (which is a nominal scale that evaluates actual, aborted, interrupted attempts, and self-injurious behavior, with no intent to commit suicide), and the fourth is the lethality of the actual attempts (scale score 0–6) [41].

The Scale of Hopelessness identifies the level of pessimism, which is directly related to the chance of developing several mental disorders and to suicide risk. The scale consists of 20 true–false questions. The total score is 20 points and each item is scored as 0 or 1 [42].

The Pittsburgh Sleep Quality Index score is a tool widely used for research and practice regarding psychiatric disorders [37]. This questionnaire interprets the perception of sleep quality in a feasible and reliable manner [37, 76]. The overall index is composed of seven components, namely subjective sleep quality (perception of sleep quality of subjects), sleep latency (time between lying on bed and sleeping), duration of sleep (sleeping period reported by the individual), sleep disturbance (sleeping problems), sleep medication (use of sleeping medications), and diurnal dysfunction (daytime sleepiness intensity). All the seven components are scored from 0 (no difficulty for the component of interest) to 3 (very bad). The scores on these components are combined to generate a global score that reflects the sleep quality and disturbances over a 1-month period. The overall score ranges from 0 to 21; if a patient reaches at least 5 points, they are diagnosed with an alteration of sleep. The higher the score the worse the quality of sleep.

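### A normality test triggers automatic log transformation of scales that include 0 or negative values, which leaves the best scores undefined and turns change in MADRS points into a ratio

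*Protocol article*

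**What the plan says.** In the protocol article, under Data analysis and power calculations, Shapiro–Wilk and Levene "tests will be used to determine normality and variance equality, respectively". The next sentence is an instruction: "Non-normal data will be log transformed". If that fails, "If the transformation does not produce a normal distribution, the effect of influential points in data analyses will be tested", and points that alter the interpretation are removed. No step returns to the untransformed scale. Linear mixed models with group and time as fixed factors and patient as random factor "will be performed for each outcome (MADRS, clinical outcomes, hippocampal volume" and the remaining outcomes.

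Elsewhere the article defines the scales to which this applies:

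- MADRS: "scores range from 0 to 60", higher being worse (Outcome measures – primary outcome).
- Columbia scale: "severity of ideation (score of 0–5"). In the same section, hopelessness is 20 items scored 0 or 1, and the Pittsburgh index runs from 0 to 21.
- Global cardiovascular score: "This ranges from less than 0 (no risk) to greater than 17" (Overall cardiovascular score).

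The abstract fixes the primary endpoint: "The primary outcome measure will be the change in depression score measured by the Montgomery-Asberg Depression Rating Scale".

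**The concern.** The rule and the scales do not fit together. A log exists only for values above 0, and low is good on all of these scales. The values with no log are therefore the best results: no depressive symptoms, no ideation, no cardiovascular risk points. Losing them is not random, and it is heaviest in whichever arm does best.

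The second problem arises even if nobody scores 0. On the log scale, group-by-time asks whether the proportional change is equal across arms. The stated primary outcome is change in the score. A significance test on the trial's own data would then decide which of the two questions the primary analysis answers.

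**Working it through.** The plan states no figure on this point, so there is none to reproduce. The scale ranges, the log rule, the mixed model and 25 patients per group come from the article. It gives no means, SDs or share of zeros, so all of those below are assumptions.

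1. **Domain.** log(x) needs x > 0. MADRS, Columbia ideation severity, hopelessness and the Pittsburgh index can equal 0; the global cardiovascular score can be negative. In the mixed model, an undefined value removes that observation. The patient's other visit stays.

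2. **Shift of scale.** Take two falls of 10 MADRS points. From 30 to 20, ln(20/30) = -0.41. From 12 to 2, ln(2/12) = -1.79. They are equal in points but differ more than fourfold on the log scale.

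3. **Does an offset cure this?** For a fall from 10 to 0 with offset c, the log change is ln(c/(10 + c)): -4.62 for c = 0.1, -3.04 for 0.5, -2.40 for 1 and -1.10 for 5. The value is now defined, but it depends on c and is still not a difference in points.

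4. **Chance of any zero.** Among 75 patients this is 1 − (1 − p)^75. With a zero share p of 1% it is 53%; with 5% it is 98%.

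5. **MADRS trigger.** Assumed: normal scores rounded and clipped to 0–60, baseline mean 25, SD 9, correlation 0.5. Means are before clipping.

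| Post mean | Post scores at 0 | Shapiro–Wilk rejects, n = 25 | n = 75 |
|---|---|---|---|
| 20 | 1.5% | 5% | 5% |
| 15 | 5.4% | 6% | 23% |
| 10 | 14.5% | 36% | 97% |
| 8 | 20.3% | 64% | 99.9% |

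With post means of 8 and 15 in two arms, dropping the zeros shrinks the raw contrast from -6.3 to -4.9 points.

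6. **MADRS power.** Assumed: 25 per arm, baseline 24 (SD 6), post means 20, 16 and 12, post SD 8, correlation 0.5. Zeros are 1–7% per arm, Shapiro–Wilk on pooled post scores rejects in roughly 10% of runs, and power is about 0.93 raw and 0.87 logged. With a responder mixture (60% against 20% responders, zeros 27% against about 10%), the test rejects in 99.9% of runs. Power then falls from 0.74 to 0.62 on complete pairs, and from 0.75 to 0.70 in the mixed model.

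7. **Columbia ideation.** Assumed: 60% have ideation at baseline, it persists in 80%, 80% and 20% (AEMC), and there are no new cases. Positive scores per arm of 25: 0.6 × 25 = 15 at baseline; after treatment 0.6 × 0.8 × 25 = 12 in C and CAE and 0.6 × 0.2 × 25 = 3 in AEMC. So 22 of 25 AEMC post scores have no log. Power is about 0.74 raw and 0.04 logged on complete pairs; in the mixed model, 0.75 and 0.07. With log(x+1) it is about 0.8. Separately, if 30% to 70% of values are 0 and the rest spread evenly over 1–5, Shapiro–Wilk at n = 25 rejects in 98% to 100% of samples. The raw power depends on the severities assumed among those with ideation; the count of undefined values does not.

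**The case against.** The best counter-argument is that an offset is a routine detail that an article leaves to the full analysis plan, so silence about it is no defect. That stands for the loss of zeros. It does not stand for the shift from points to ratios (step 3), nor for the rule itself, which is stated as an instruction for every outcome. A later plan that kept MADRS untransformed after a failed normality test would contradict it.

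A log analysis is also not always the weaker one. If improvement is proportional (assumed post/pre ratios 0.8, 0.7 and 0.5, log-SD 0.5), the log has power 0.86 against 0.75 raw. This stands. The article also reports means with SDs, Cohen's d and a count of patients in remission, and that count keeps a patient who scores 0. This softens the reporting but does not alter the primary test.

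A reader might infer four stronger things that the documents do not support:

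- *The rule will usually fire for MADRS.* That needs post-treatment means near 8 to 10 or a mixture of responders and non-responders. The article gives no such distribution, and remission below 10 points does not mean a score of 0.
- *Whole patients drop out.* In the planned mixed model only the observation is lost. The patient is lost in the fallback ANCOVA or if complete pairs are required.
- *False positives rise.* With equal mean change, one set of assumptions gave rejection of 6% raw and 24% logged; another gave 7% and 6%. The result depends on the parameters.
- *Every improving patient becomes undefined because change is negative.* The analysis section models scores by group and time; it does not log change scores.

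**Conclusion.** The point holds in a conditional form. The article fixes a transformation rule that cannot be carried out as written on several of its own scales. Where it can be carried out, it moves the primary comparison away from change in MADRS points.

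For Columbia ideation the failure is near certain, given any substantial share of zeros and no offset: the test loses almost all its power. With log(x+1) the power returns, though on a different scale. For MADRS the size ranges from small (about 0.93 to 0.87, with a trigger in roughly 10% of samples) to larger when many patients score near 0, and it can reverse if effects are proportional. All of these sizes rest on assumed distributions; the scale mismatch and the shift to ratios do not. Confidence is high for the rule and for ideation, and moderate for the practical effect on MADRS. The change should be made, but the trial does not stand or fall with it.

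**What to change.** In Data analysis and power calculations, replace the log rule with an analysis scale stated in advance for each outcome, so that no normality test chooses it:

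- Restrict log transformation to strictly positive measures, such as BDNF, triglycerides and Trail Making time.
- Analyse MADRS, hopelessness, the Pittsburgh index and the global cardiovascular score untransformed, and report MADRS as a difference in points.
- Judge normality on model residuals. If it fails, robust or bootstrap standard errors are one option.
- Analyse Columbia ideation severity by a method that keeps the zeros, such as an ordinal model or a rank test.

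The cost is a short change of text, slightly more analysis work, and possibly some lost power if effects are truly proportional. No extra patients or data are needed.

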**Discussion:**

This study was selected in the call of public policy programs for the Brazilian Unified National Health System – “PPSUS 2015”. To our knowledge, this is the first pragmatic trial to test the effect of adding AEMC to the pharmacological treatment of patients with depression and to evaluate the possible reductions in depression symptoms and healthcare costs.

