#### Treatment costs

Treatment cost for each patient will be determined using the methods described by Codogno [50, 54]. At the end of the trial, the demands for services and medicines recorded on medical records throughout the 6 months of the intervention period will be considered. The following information will be obtained: medicines supplied to the patient, laboratory tests performed, and the number of consultations throughout the intervention period. In addition, patient costs will encompass the cost of administrative and maintenance services related to the BHU where the procedures will be performed. The costs stipulated for these services and the number of patients attended will be added to the costs of each patient, according to the number of days that they visited the BHU over the 6-month period. In order to transform the procedures into actual currency, the values informed by the Municipal Health Department for the year 2018 will be used.

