## Discussion

The present study has the objective to verify if patients with depression randomized into one of two physical exercise interventions (AEMC or CAE) combined with traditional drug treatment will present distinct improvements in depression symptoms (MADRS). In addition, different outcomes commonly altered by depression and with the potential to be reversed by physical exercise (e.g., cognitive function, hippocampal volume, brain-derived neurotrophic factor, sleep parameters, cardiovascular risk parameters, suicidal behavior, functionality, and treatment costs) will be evaluated.

From an operational standpoint, a pilot study involving 45 healthy elderly people was carried out in 2017, considering interventions with AEMC (two levels) and CAE (stationary cycling). Data from the pilot study are under analysis, but greater improvements with regards to cognitive and motor aspects were observed in the group undergoing exercises with greater motor complexity. In addition, training interventions produced very high exercise adherence (95%), which may be a differential, considering the difficulties in maintaining adherence during a traditional physical exercise program [89]. The main objective of this pilot study was to establish training routines and assessments and to provide logistical experiences between the parties involved (BHU, University, institutions involved in implementing training interventions and evaluations, and researchers) for the development of the proposal with patients with depression.

To our knowledge, this is the first study to test the effect of adding physical exercise to traditional treatment in patients with depression in a primary health care setting in Brazil. In addition, the use of aerobic exercises with insertion of activities with progressively higher motor complexity has not yet been tested in this population. Considering that exercises with high motor complexity may promote changes in cortical activation [90] and possibly increase the volume of associated encephalic structures (i.e., hippocampus) [27] in healthy individuals, assessing such adaptations in patients with depression is of great interest for clinical practice and public policies.

Finally, determining the impact of physical exercise programs on the treatment costs of patients with depression in Brazil may lead to new polices on how to treat them while decreasing the associated costs [2].

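### If treatment costs are log transformed under the general rule, the test compares geometric means, while the stated policy question concerns mean cost per patient; a minor point on one secondary outcome

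*Protocol article*

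**What the plan says.** All analysis rules are in the section on data analysis and power calculations. It names Shapiro–Wilk and "Levene’s tests will be used to determine normality and variance equality, respectively", and then states "Non-normal data will be log transformed". No outcome is exempt. If the log does not give normality, influential points are examined, and "If influential points change the interpretation of the results, they will be manually removed". The list of outcomes for the linear mixed models ends with "cardiopulmonary parameters, lipid profile, and treatment costs". A significant F value leads to Tukey-adjusted comparisons. Results are shown as mean and SD. The section gives no rule for back-transformation and no action to follow from the variance test.

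The Treatment costs section defines the outcome as each patient's medicines, laboratory tests and consultations over the 6-month intervention period, plus health-unit overhead by days visited. These are priced in money: "In order to transform the procedures into actual currency, the values informed by the Municipal Health Department for the year 2018 will be used".

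The purpose is economic. The abstract says the trial will "evaluate the possible reductions in depression symptoms and healthcare costs". The main Discussion gives as a policy goal "determining the impact of physical exercise programs on the treatment costs of patients with depression in Brazil". The ethics section adds a final report aimed at management of the public health system.

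**The concern.** A linear model fitted to log cost estimates differences in mean log cost, which are ratios of geometric means on the original scale. What a payer spends on a group of patients is the arithmetic mean times the number of patients. The two kinds of ratio are the same only if log costs have the same spread in each arm.

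If the spreads differ, the P value and the printed means answer different questions. With equal mean costs, the arm with the wider log spread has the lower geometric mean and looks cheaper. If exercise instead lowered mean cost by removing a few heavy users, its spread would shrink and the log-scale test could miss the saving. The fallback rule adds to this, because the influential points open to removal may be the high-cost patients who drive mean cost.

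**Working it through.** **Inputs from the article.** Three groups (control, CAE, AEMC); 25 patients per group; significance at P ≤ 0.05; F test, then Tukey; one cost total per patient over 6 months. The article gives no cost mean, SD or distribution, so there is no cost figure to reproduce.

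**Assumption.** Costs are lognormal, with log-SDs from 0.5 to 1.0 in the main table. This is not in the article.

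**Step 1: would the log rule apply?** In simulated two-group comparisons with 21 or 25 per group and log-SDs from 0.5 to 1.4, Shapiro–Wilk on the raw-cost residuals rejected normality in 83% to 100% of trials. If costs are skewed to this degree, the rule nearly always applies.

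**Step 2: size of the mismatch.** For a lognormal cost, the arithmetic mean is exp(μ + s²/2) and the geometric mean is exp(μ). At equal arithmetic means, the geometric mean ratio (wider-spread arm over narrower) is exp(−(s₂² − s₁²)/2):

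- 0.6 vs 0.8: exp(−(0.64 − 0.36)/2) = exp(−0.14) = 0.869, an apparent saving of 13%.
- 0.6 vs 1.0: exp(−(1.00 − 0.36)/2) = exp(−0.32) = 0.726, an apparent saving of 27%.
- 0.5 vs 1.0: exp(−(1.00 − 0.25)/2) = exp(−0.375) = 0.687, an apparent saving of 31%.
- Equal log-SDs: exp(0) = 1, no discrepancy.

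The reverse case uses the same identity. If geometric means are equal and log-SDs are 1.0 (control) and 0.5 (exercise), mean cost in the exercise arm is 1/1.455 = 0.687 of control. That is a true 31% saving for which the log-scale difference is zero.

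**Step 3: how often the test would reject.** 20,000 simulated three-arm trials per scenario, 25 per group, equal true arithmetic means, one-way F test on log cost, then Tukey. Cost is a single total per patient, so the group comparison reduces to this form. Where a range is shown, the upper end has one arm with the wider spread and the lower end has two such arms. An affected pair is one whose two spreads differ; the equal-spread row covers any pair.

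| Log-SDs | Per affected pair (F then Tukey) | Overall F test |
|---|---|---|
| 0.8 in all arms | about 2% | about 5% |
| 0.6 vs 0.8 | 4–6% | 9–11% |
| 0.6 vs 1.0 | 12–21% | 23–31% |
| 0.5 vs 1.0 | 17–32% | 32–43% |

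Nearly all rejections in the affected pairs go one way, with the more variable arm appearing cheaper.

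**Step 4: does the planned variance test protect?** In the two-group runs with unequal spread, Levene's test on log cost rejected in about 22% to 82% of trials. The article attaches no consequence to a rejection.

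**The case against.** The strongest case against is that the harm needs unequal log spread, and nothing in the article points to it. If exercise leaves the whole cost distribution unchanged, randomisation makes the arms alike and the log-scale test is valid. A false saving needs exercise to widen the spread while leaving the mean unchanged, which is a particular pattern. The skew itself is also undocumented: the listed items are primary-care medicines, tests, consultations and overhead, with no hospital admissions. All of this stands, and it limits the point to what can happen under stated assumptions.

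A reader might infer higher error rates from a simple two-arm t test on log cost, which rejects in about 11%, 27% and 38% of trials in the three unequal scenarios. That is not the planned test. With three arms, F and Tukey, the per-pair rates are lower, and in the mildest scenario the excess is small.

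A reader might also take mean treatment cost to be what the health system pays overall. The Treatment costs section does not list the cost of the exercise programme, so neither scale gives the net budget effect.

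Two further objections carry part of the weight. Printed means and SDs could show a discrepancy, but the P value would still belong to the log scale. The choice of cost estimator is often left to an analysis plan; here, however, the article states a rule without exception and lists costs among the outcomes analysed.

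**Conclusion.** The point holds as a minor one on one secondary outcome. As written, the log rule would probably move the cost comparison onto geometric means if costs are skewed, and that is not the quantity the policy aim needs. With equal log spread there is no error. With unequal spread, the per-pair rejection rate at equal mean cost runs from 4–6% to 17–32% over the scenarios shown, against about 2% with equal spread. These figures rest on assumed lognormal costs, assumed log-SDs and 25 analysed patients per group. The documents do not support the stronger claim that the trial will report a false saving: that requires skewed costs and a wider spread in the exercise arm, and neither is documented. The primary outcome, MADRS, is not touched by this point.

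**What to change.** Exempt treatment costs from the log-transform rule and from the removal of influential points. Make the main cost comparison the between-group difference in arithmetic mean treatment cost per patient, in currency, with a bootstrap 95% confidence interval and all high-cost patients kept. A log-scale analysis may stay as supportive, labelled as a ratio of geometric means. Describe the result as treatment cost as defined in the Treatment costs section, not as net health-system spending.

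This needs a change of wording and routine computation, and no new data. It has three downsides:

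- The interval will be wider.
- Power is somewhat lower if the true effect is proportional. For a 30% saving with 25 per group in a two-arm comparison, power is about 34% on the log scale against 26% for a Welch test on raw cost at log-SD 0.8, and about 24% against 15–16% at log-SD 1.0.
- Error control on the raw scale is slightly imperfect at this size. The Welch test rejected in about 5%, 7% and 9% of two-arm trials in the three unequal scenarios.

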### Randomization

After baseline assessments, a blind researcher will classify patients into terciles regarding their MADRS score and number of previous depressive episodes. Subsequently, patients from each tercile will be randomly assigned to the control (C), CAE, or AEMC groups. A one-way ANOVA will test for similar initial values for MADRS scores and number of depressive episodes between groups (*P* > 0.05). The Principal Investigator will be blinded to all of the procedures to perform the randomization and analyses.

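### Influential points are deleted because they change the conclusion, so for outcomes still non-normal after log transformation the reduced data always decide the result and the 5% level is not held

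*Protocol article*

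**What the plan says.** The section on data analysis and power calculations sets out a sequence:

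1. Distribution checks: "The Shapiro–Wilk and Levene’s tests will be used to determine normality and variance equality, respectively".
2. Transformation: "Non-normal data will be log transformed".
3. If that fails: "If the transformation does not produce a normal distribution, the effect of influential points in data analyses will be tested".
4. Then: "If influential points change the interpretation of the results, they will be manually removed".

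The sequence covers every outcome, the primary one among them: "Linear mixed models having group and time as fixed factors and patients as a random factor will be performed for each outcome". One threshold applies throughout; "the level of significance adopted in the present study for all analyses will be" P ≤ 0.05.

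The article does not define an influential point, set a cut-off, require a data error before a value is dropped, or say that the full-data result remains primary. The study design section says that the researchers who run the statistical analyses are blinded to allocation.

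**The concern.** An influence check normally asks whether a conclusion is fragile. If it is, the full-data result stands and the fragility is reported. Here a finding of fragility causes the points to be removed. A correctly measured MADRS value from a patient who did very well or very badly can be dropped for no other reason than that it matters to the answer.

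The P ≤ 0.05 threshold is calibrated for an analysis chosen without sight of the result, and this rule chooses the data set by the result. Removing extremes also shrinks the standard deviation, which can enlarge the Cohen's d values that the same section promises for each outcome. With 21 evaluable patients per group in the power calculation, a few values can decide a comparison.

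**Working it through.** **Logic, before any numbers.** Take an outcome that has reached step 4.

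| Full data | Reduced data | What the rule does | Reported |
|---|---|---|---|
| significant | significant | keep points | significant |
| significant | not | remove | not |
| not | significant | remove | significant |
| not | not | keep points | not |

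The last column always equals the second. The full randomised data never prevail when the two disagree. Hence

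false-positive rate = P(step 4 not reached and full data significant) + P(step 4 reached and reduced data significant).

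**Inputs from the article.** Three groups; 21 evaluable and 25 randomised patients per group; significance level 0.05; a Shapiro–Wilk check ahead of the deletion step.

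**Assumptions, because the article fixes none of these.**
- Shapiro–Wilk is applied at 0.05 to model residuals.
- A change of interpretation means that significance at 0.05 flips, in either direction.
- Four influence criteria are tried: Cook's D > 4/n, absolute standardised residual > 2, absolute studentised residual > 3, and 1.5 × IQR within group.
- Five error distributions are tried: normal, t with 5 df, t with 3 df, normal with 10% contamination at 4 × SD, and exponential.
- The log step is not modelled. The non-normal cases stand for outcomes where it has failed.

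**Test.** F-test of group on change scores, which equals the group-by-time test with two complete time points. There were 10,000 trials per setting with no true effect; the simulation standard error near 5% is √(0.05 × 0.95 / 10,000) ≈ 0.2 points.

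**Reproducing the nominal level.** With normal errors and all points kept, theory gives exactly 5%. The simulation gave 5.2% (25 per group) and 5.0% (21 per group).

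**The rule as written** (ranges over both group sizes):

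| Errors | Step 4 reached | All points kept | Cook's D or residual criteria | IQR criterion |
|---|---|---|---|---|
| normal | 4.8–5.0% | 5.0–5.2% | 5.2–5.7% | 5.5–5.6% |
| t, 5 df | 38.6–45.0% | 4.7–5.1% | 6.2–7.9% | 8.3–8.5% |
| t, 3 df | 69.8–76.7% | 4.3–4.4% | 5.9–8.5% | 9.5–10.0% |
| contaminated | 82.9–88.0% | 4.5–4.6% | 6.1–7.5% | 9.3% |
| exponential | 99.8–100% | 4.5–4.9% | 6.7–8.6% | 21.7–21.8% |

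**Why a two-way rule still inflates.** Take t with 3 df, 21 per group, Cook's D. The full-data rate is 4.32%, the conclusion flips in 5.88% of trials, and the reported rate is 8.18%. The net gain is 8.18 − 4.32 = 3.86 points. Flips towards significance are (5.88 + 3.86)/2 = 4.87% and flips away are (5.88 − 3.86)/2 = 1.01%. Trimming extremes lowers the residual variance, so the flips run nearly five to one towards significance.

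**Fixed number of points instead of a cut-off.** A separate run (6,000 null trials, 21 per group, same Shapiro–Wilk condition) removed the largest residuals when the decision flipped. For t with 5 df, t with 3 df and exponential data, it gave 5.6–6.3% with one point removed and 8.1–10.6% with up to three.

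**The log step on bounded scales.** For MADRS, "The higher the score, the greater the presence of depressive symptoms; scores range from 0 to 60". Hopelessness runs from 0 to 20 and Columbia ideation severity from 0 to 5. A plain logarithm is undefined at 0, and no offset is stated.

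**The case against.** Several points count against a broad version of this criticism.

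- **The rule is conditional.** It acts only after both the normality check and the log transformation have failed. A reader might infer that every outcome is affected, or that even normal data would show rates well above 5%. Without the condition, normal data do give 8.5% (one point) and 15.2% (up to three). With it, as the article is written, they give 5.5% and 5.9% at 21 per group, and 5.2% and 5.4% at 25. The larger figures describe a rule that the plan does not contain. Nor does the article show that MADRS will reach the deletion step; it only allows it.
- **The rule is symmetric.** It also deletes points that created significance. Rates computed by keeping only deletions towards significance (6.8 to 11.3% in most non-normal settings) describe misuse, not this plan. The symmetric rule still raised the error in every non-normal setting tried.
- **Analysts are blinded.** This limits steering towards a particular arm. It does not remove the trigger, because a P value can be read with the groups coded A, B and C.
- **Points, not patients, are removed.** In a mixed model a patient who loses one observation can still contribute the other, so the text does not support saying that randomised patients are lost outright.
- **Details may sit in a fuller plan.** A definition of influential, or an offset for zeros, could well be there. Neither would repair a trigger that depends on the conclusion. The zero problem is minor in any case: enrolled patients must meet criteria for major depression, so baseline MADRS zeros are unlikely, although post-treatment zeros are possible.

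**Conclusion.** The deletion rule is wrong as written. That conclusion follows from the four-case table alone and needs no simulation.

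The size is less certain, since it rests on assumed distributions and criteria, and no single figure can be given. For outcomes that reach the deletion step, the false-positive rate is about 6% with one point removed and about 6 to 10% under common cut-offs. It is about 22% only for exponential data with the IQR criterion. Keeping all points gives 4.3 to 5.2% across the settings tried. The one-point excess is small: its low end of 5.6% lies only about two simulation standard errors above 5%, with √(0.05 × 0.95 / 6,000) ≈ 0.28 points. Outcomes with normal errors stay near 5%.

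The point should be corrected before analysis, because the rule can reach the primary outcome and lets the result choose the data set.

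**What to change.** Delete the removal sentence and state instead:

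- Values are excluded only for documented data errors, decided blind to arm.
- All valid values stay in the primary analysis of every outcome.
- An analysis without influential points, using a named criterion and cut-off fixed before unblinding, is reported beside it as a sensitivity analysis only.
- Distributional assumptions are checked on model residuals. If these are clearly non-normal, a robust, rank-based or resampling method named in advance is used in place of deletion.
- As a minor addition, the log step carries a stated offset, or an alternative, for scales that can be 0.

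The choice among robust, rank-based and resampling methods is open; what matters is that it is made beforehand. The cost is a change of wording and a few lines of analysis code, with no new data or patients. The trial status section reports that no participants had been included, so at that stage the change could be made before any data existed.
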